## Abstract

**Background:**

Neurosyphilis may cause irreversible neurological sequelae. First-line treatment consists of penicillin G, with ceftriaxone being an alternative treatment in patients allergic to penicillin. The lack of clinical data comparing the efficacy of these two drugs indicated the need for comparative clinical trials to improve national treatment guidelines in China.

**Methods/design:**

In this multicenter randomized controlled clinical trial, 290 patients newly diagnosed with neurosyphilis will be randomized 1:1 to treatment with aqueous crystalline penicillin G (ACPG) or ceftriaxone. Patients will be treated with standard regimens of ACPG or ceftriaxone according to Chinese National Guidelines and will be followed up for 12 months. All clinical parameters will be assessed at baseline and at follow-up 3, 6, 9, and 12 months later. The primary outcomes will include cerebrospinal fluid (CSF) white blood cell (WBC) count, serological efficacy, and clinical efficacy. The secondary outcomes will include CSF protein concentrations, Mini-Mental State Examination (MMSE) scores, imaging results, recurrence, and time to recovery from neurosyphilis. Adverse events will be monitored and recorded during the trial.

**Discussion:**

This trial will provide clinical data to determine whether ceftriaxone is non inferior to ACPG in treating neurosyphilis and will provide evidence for the improvement of treatment guidelines.

**Trial registration:**

Chinese Clinical Trial Registry ChiCTR2100047164. Registered on 9 June 2021 and updated on 23 November 2021.

## Background

Neurosyphilis is a serious manifestation of syphilis that may cause irreversible damage to the central nervous system (CNS) and even death. The epidemiology of neurosyphilis largely parallels that of syphilis [1, 2]. The reported incidence of syphilis has increased from 30.93 per 100,000 persons in 2014 to 38.37 per 100,000 persons in 2019, an annual increase of 4.41% [3]. The disease burden of neurosyphilis has likely increased to a similar extent, emphasizing the need to eliminate the health hazards caused by neurosyphilis.

Early and adequate treatment of patients with neurosyphilis is the basis for the prevention of neurological sequelae. Penicillin G was first shown in 1940 to be effective in the cure of neurosyphilis [4], and aqueous crystalline penicillin G (ACPG) is still recommended by most guidelines as a first-line treatment for neurosyphilis [5, 6]. Following treatment, however, some patients, especially those with late neurosyphilis, experience persistent symptoms, or their serum or cerebrospinal fluid (CSF) shows no response to nontreponemal tests [7, 8]. Moreover, standard treatment regimens are hard to follow completely, and the long hospital stay and short intervals between ACPG treatments place a considerable burden on patient care [9].

Approximately 10% of patients with neurosyphilis report having an allergy to penicillin [10]. Because ceftriaxone is active against *Treponema pallidum* in vitro, with good blood–brain barrier penetration, ceftriaxone is utilized as an alternative to ACPG to treat neurosyphilis in patients with a penicillin allergy [11]. Ceftriaxone may also be used as outpatient parenteral antimicrobial therapy (OPAT) to reduce the length of hospital stay, providing both economic and quality-of-life benefits to patients with neurosyphilis [12]. A prospective, single-center clinical trial comparing ACPG and ceftriaxone for the treatment of human immunodeficiency virus (HIV)-infected patients with neurosyphilis found no significant differences in serological and clinical efficacy of these two drugs [13]. The conclusions of that study, however, were limited by its small sample size, low number of events, and incomplete data regarding outcomes [14]. Although a recent large, multicenter retrospective study in France found no difference in efficacy between ceftriaxone and ACPG [12], there is a lack of high-quality clinical data to confirm these results [15].

In summary, we designed a non-inferiority randomized controlled trial to compare the efficacy of ceftriaxone with ACPG in the treatment of neurosyphilis. If the findings show that ceftriaxone is non-inferior to ACPG, these will provide evidence for the increased use of ceftriaxone in clinical settings and the improvement of guidelines for the treatment of neurosyphilis. Long-term clinical evaluation may determine whether the efficacy of ceftriaxone is equivalent or superior to that of ACPG.

## Methods

### Study design

This prospective, multicenter, non-inferiority, randomized, controlled trial was designed to compare the efficacy of ACPG and ceftriaxone in the treatment of patients with neurosyphilis. Patients will be randomized 1:1 to treatment with ACPG or ceftriaxone. Clinical data will be recorded prior to treatment and 3, 6, 9, and 12 months after treatment. The flow diagram of this trial is shown in Fig. 1 and its schedule is shown in Fig. 2. This trial was designed in accordance with the World Health Organization (WHO) Trial Registration Data Set (TRDS) and all relevant items are present in this protocol.

**Fig. 1 Fig1:**
[figure not shown]
Flow diagram of the study design. Abbreviations: CSF, cerebrospinal fluid; RPR, rapid plasma reagin

**Fig. 2 Fig2:**
[figure not shown]
Participant timeline: schedule of enrolment, interventions, and assessments. Abbreviations: CSF, cerebrospinal fluid; RPR, rapid plasma reagin. MMSE, Mini-Mental State Examination

### Participants

This trial was organized by the Institute of Dermatology, Chinese Academy of Medical Science (the head research center) and will be conducted at five medical centers: the Fifth People’s Hospital of Suzhou, the Second Affiliated Hospital of Nanjing Medical University, Chongqing First People’s Hospital, Xi’an North Hospital, and Dalian Dermatology Hospital. Chinese inpatients with newly diagnosed neurosyphilis will be recruited, and all patients will provide written informed consent before treatment and will be randomized into different groups. The trial protocol was reviewed and approved by the Medical Ethics Committee of the Chinese Academy of Medical Sciences Institute of Dermatology and National Center for STD Control in Nanjing (approval number: 2020-KY-022) and has been registered in the Chinese Clinical Trial Registry (ChiCTR2100047164) on 9 June 2021 and updated on 23 November 2021.

#### Inclusion and exclusion criteria

Patients newly diagnosed with neurosyphilis will be enrolled. Criteria for the diagnosis of neurosyphilis include a history of syphilis infection at any stage, with or without CNS manifestations, and laboratory findings that included abnormalities on routine CSF tests, such as elevated white blood cell (WBC) counts, defined as ≥5 cells/mL in the absence or >20 cells/mL in the presence of HIV infection, or protein concentrations of >500 mg/L, and excluding other diseases that may account for these abnormalities [5, 6, 16]. For inclusion, patients had to meet one or more of the following criteria: (i) reactive CSF on Venereal Disease Research Laboratory (VDRL) or fluorescent treponemal antibody absorption (FTA-ABS) tests and (ii) reactive CSF on rapid plasma reagin (RPR)/tolulized red unheated serum tests (TRUST) or Treponema pallidum particle assay (TPPA) tests. Detailed inclusion and exclusion criteria are shown in Table 1. The attending physician of each patient will be responsible for assessing inclusion and exclusion criteria.

**Table 1 Tab1:** Inclusion and exclusion criteria

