#### Primary outcomes

##### CSF white blood cell (WBC) count

CSF-WBC count is a sensitive indicator of the curative effect of interventions on neurosyphilis, with Chinese National Guidelines recommending that CSF-WBC count be assessed at 6-month intervals. In this trial, a significant reduction in CSF-WBC count or return to a normal range (<5×10^6^/L in the absence or ≤ 20×10^6^/L in the presence of HIV coinfection) after treatment was defined as effective.

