##### Nonresponse to treatment

Nonresponse will be defined as persistent symptoms, a sustained titer of CSF-VDRL/RPR (i.e., the titer did not decrease by two dilutions or showed reversion to nonreactivity), or an elevated CSF-WBC count during the 12-month follow-up.

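### The CSF white-cell cut-offs for diagnosis and for the primary outcome are in units that differ by a factor of 1,000, so one count can be both elevated and normal

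*Protocol article*

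**What the plan says.** The protocol article defines the CSF white-cell threshold in two places.

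- **Inclusion and exclusion criteria.** An elevated count is "defined as ≥5 cells/mL in the absence or >20 cells/mL in the presence of HIV infection". It is given as an example of an abnormal routine CSF test, with an alternative in the same sentence: "or protein concentrations of >500 mg/L". A serological requirement follows, introduced by "For inclusion, patients had to meet one or more of the following criteria", and both listed criteria are reactive CSF tests. Attending physicians assess eligibility.
- **Primary outcomes, CSF white blood cell (WBC) count.** Treatment is effective on "a significant reduction in CSF-WBC count or return to a normal range", and the normal range is "<5×10^6^/L in the absence or ≤ 20×10^6^/L in the presence of HIV coinfection".

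Two secondary outcomes depend on the same distinction without giving a number or a unit. Nonresponse to treatment includes the phrase "or an elevated CSF-WBC count during the 12-month follow-up". Recurrence of neurosyphilis refers to a count that becomes normal and then abnormal again. Table 1 gives no white-cell cut-off, and nothing else in the article reconciles the two units.

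**The concern.** The two definitions should be two sides of one line: a patient above it at diagnosis has an abnormal count, and a patient brought below it has returned to normal. In the printed units there are two lines, three orders of magnitude apart, and every count between them falls on both sides.

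Three uses are affected if the printed units are followed. A site could treat a count as an abnormality supporting the diagnosis although the outcome section calls it normal. That patient would already be in the outcome's normal range before treatment. And at follow-up the same count could be scored effective on the primary outcome and, if elevated is taken from the diagnostic sentence, as nonresponse on the secondary one. The diagnostic sentence is the only place where the article defines elevated, so that last reading is a natural one.

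**Working it through.** **Inputs.** The diagnostic cut-offs are 5 and 20 cells/mL (Inclusion and exclusion criteria). The outcome limits are 5×10^6/L and 20×10^6/L (CSF white blood cell (WBC) count).

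**Conversion.** 1 L = 1,000 mL, so *c* cells/mL = *c* × 10^3 per L, and *c* × 10^6/L = 1,000 × *c* cells/mL = *c* cells/µL.

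| | Elevated at diagnosis, as printed | Same, in 10^6/L | Normal for the outcome, as printed | Same, in cells/mL | Ratio of limits |
|---|---|---|---|---|---|
| No HIV | ≥5 cells/mL | ≥0.005 | <5×10^6/L | <5,000 | 5,000 / 5 = 1,000 |
| HIV | >20 cells/mL | >0.02 | ≤20×10^6/L | ≤20,000 | 20,000 / 20 = 1,000 |

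**Overlap as printed.** Without HIV, any count from 5 to just under 5,000 cells/mL is both elevated and normal. With HIV, the same holds for any count above 20 and up to 20,000 cells/mL.

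**Example, no HIV.** A count of 1×10^6/L is 1,000 cells/mL. That is 1,000 / 5 = 200 times the diagnostic cut-off, and 1,000 / 5,000 = one fifth of the outcome limit.

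**Same unit in both places.** If both used 10^6/L, the pairs would be ≥5 against <5 without HIV, and >20 against ≤20 with HIV. Each pair covers every count once, with no overlap and no gap. Numbers, inequality signs and HIV split already agree, and only the unit does not. This is why a slip in the diagnostic sentence (mL where µL was meant) is the likely explanation, although the article does not say so.

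**Does anything else depend on the cut-off?** The Sample size section uses a risk ratio of 1.5, a factor of 7.85, a success rate of 85% and a loss of 20%:

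- events: 7.85 × (1 + 1.5)^2 / (1 − 1.5)^2 = 7.85 × 25 = 196.25 (stated: 196);
- participants: 196 / 0.85 = 230.6 (stated: 230);
- with loss: 230 / (1 − 0.20) = 287.5, so 288 (stated: 290, which is 5 × 58).

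None of these inputs uses a white-cell threshold, so the planned size does not change.

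**The case against.** The strongest reply is that the intended meaning can be recovered. With matching numbers and complementary signs, a clinician or laboratory would probably read the diagnostic cut-off in the outcome's unit. The outcome section is coherent in itself, so scoring a return to normal does not inherit the slip. A µ turned into an m in typesetting or text conversion cannot be excluded altogether, but Greek letters elsewhere in the article are intact and the unit is printed twice in the same clause. This reply stands as a reason to call the point a slip rather than a deliberate lower threshold. It does not remove the contradiction, because physicians at five centres apply the diagnostic definition and no other text corrects it.

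A reader might infer two stronger things that the article does not support.

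- *That almost anyone with detectable CSF cells can enter.* The count is one example among the routine CSF abnormalities. The diagnosis also needs a history of syphilis and the exclusion of other causes, and inclusion needs a reactive CSF test. Even a literal reading loosens only one component of a composite diagnosis.
- *That the slip biases the trial towards non-inferiority by admitting patients who count as effective from the start.* This would need sites to apply the literal unit and some patients to enter only because of it. The article gives no basis for a number of such patients, so no effect on response rates or on the 10-point margin can be computed. Nor is the mechanism peculiar to the unit: with the units aligned, a patient who qualifies on protein alone can still have a normal count at baseline. That is a separate design question.

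**Conclusion.** The inconsistency is real, and its size is exact: a factor of 1,000 in the limits, with and without HIV. It is most likely a unit slip in the diagnostic sentence. That judgement rests on the match of numbers and signs, not on any statement in the article.

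If the text is taken literally, the same count can be elevated for diagnosis and normal for a primary outcome, and the nonresponse definition is ambiguous. The practical effect on entry is limited by the other diagnostic and serological requirements, the sample size is untouched, and the effect on the results cannot be quantified from the document. The case for correcting it is that a diagnostic threshold in use at five centres contradicts the outcome definition, not that a bias has been shown.

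**What to change.** 1. Reconcile the cut-offs in Inclusion and exclusion criteria and in the CSF white blood cell (WBC) count outcome, and state both in one unit. Elevated and normal should then be exact complements for patients without HIV and for patients with HIV.
2. State that Nonresponse to treatment and Recurrence of neurosyphilis use this same definition.
3. Confirm that the CRF and the site SOPs carry the reconciled unit. They are not shown, so nothing indicates that they contain the error. Recruitment began on 1 December 2021, so if a site did use the printed mL unit, the check should extend to patients already enrolled there on the white-cell criterion.

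The cost is a one-line correction, a cross-reference in two outcome definitions, and a document check. None of this changes the sample size or the analysis. It also does not settle how the primary outcome should handle patients who enter on protein with a normal baseline count, which needs its own decision.

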**Inclusion criteria**	
1. First-diagnosed neurosyphilis patients (untreated patients referred from other hospitals may also be included)	
2. Age of 18 to 70 years old	
3. No intravenous or intramuscular injection of antibiotics for the treatment of neurosyphilis within the last 3 months (penicillin G, ceftriaxone, etc.)	
4. Patients having voluntarily signed the informed consent form	
**Exclusion criteria**	
1. Allergy to aqueous crystalline penicillin G or ceftriaxone	
2. Exclusion from other central nervous system diseases or conditions that might cause abnormalities in cerebrospinal fluid tests	
3. Pregnancy and lactation	
4. Serious adverse reactions during treatment	
5. Standardized treatment not carried out strictly according to the treatment regimen, or inability to follow up as required	
6. Patients who require the termination of treatment, for which the efficacy and adverse reactions cannot be evaluated, or patients who request withdrawal from the study	
7. Patients with incomplete clinical data that cannot be counted	

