### Management of data and biological samples

Each research center should assign investigators to collect clinical information from patients, including demographic characteristics (patient name, ID number, telephone number, and other identifying information, which will be kept anonymously), history of sexually transmitted disease (STD) infection and treatment, lifestyle, information acquired at each visit (including clinical manifestations, results of laboratory tests and auxiliary examinations, and diagnosis and treatment information), and the occurrence and management of adverse events. All adverse event data will be systematically collected using standardized coding MedDRA, with the details recorded in a case report form (CRF). At each research center, several researchers will be assigned to call the enrolled patients to remind them of each follow-up visit. Real-time telephone consultations and psychological counseling can be provided after treatment to improve follow-up compliance. All data on each patient will be double entered into an electronic CRF (eCRF). Data from patients who did not complete follow-up and voluntarily withdrew from the study will be retained with other data.

At the end of the trial, the investigators at each branch center will submit the eCRFs of all patients to the head research center. Information on the eCRF for each patient should be complete and signed. All data will be submitted to the Data Monitoring Committee (DMC) of the head research center and uploaded to the Resman Clinical Trial Management Public Platform (http://www.medresman.org.cn/pub/cn/proj/search.aspx) within 6 months after completion of the trial. The results of the trial will be published in a peer-reviewed journal. Documents of all participants will be preserved for at least 10 years after publication, allowing the original data to be accessed if necessary. The clinical data will be used in future studies with the consent of the participants.

The specimens (blood and CSF) used in this trial will be collected by hospital laboratory staff for diagnosis and assessment of the clinical efficacy of treatments for neurosyphilis. After analysis, the samples will be destroyed and will not be kept for future studies.

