### Statistical analysis

All statistical analyses will be performed using SPSS 21.0 statistical software by biostatisticians blinded to group assignment. Missing data for the primary outcome will be imputed using the multiple imputation method. Serum and CSF RPR titers will be analyzed after log_2_ conversion. Normally distributed continuous variables in the two groups will be compared by *t* tests, and categorical variables will be compared by the *χ*^2^ test or *Fisher’s *exact test, as appropriate. Nonparametric variables will be compared by rank sum tests. The correlation between serum and CSF RPR titers will be analyzed using Spearman’s rank correlation tests. Based on the assumption that there are no obvious correlations between primary outcomes and that it will be impossible to determine which outcome has greater weight, the weights of these primary outcomes will be evaluated using the “Experts Scores” algorithm, with “overall response” to treatment evaluated according to the total efficacy scores from these primary outcomes. The results of each primary outcome will also be evaluated separately. The non-inferiority margin will be set at 10 percentage points for the absolute difference between the two groups. If the standard for non-inferiority is reached, all primary and secondary outcomes will be tested for superiority (*P*<0.05). Non-inferiority will be considered reached if conclusions drawn from the intention-to-treat (ITT) population, consisting of all patients who met the inclusion criteria, were randomized, and started treatment, and the per-protocol population, consisting of all patients with good compliance and who followed the protocol to completion of the treatment regimen, are consistent. Univariate analyses will be performed to identify potential factors associated with the treatment outcome, with variables having a *P* value ≤0.10 in univariate analyses included in a multivariate logistic regression model. Odds ratios (ORs), adjusted ORs (aORs), and their 95% confidence intervals (CIs) will be calculated. A two-sided *P value* <0.05 will be considered statistically significant. Because the efficacy and safety of ceftriaxone and ACPG are clear and both are recommended by Chinese National Guidelines, this trial will not include interim analyses.

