## Discussion

Penicillin G is regarded as the first-line drug for the treatment of neurosyphilis based on the pharmacokinetics of available drugs, their effect on *T. pallidum* in vitro, laboratory considerations, biological plausibility, expert opinions, case studies, and clinical experience [5]. Ceftriaxone is an alternative to penicillin G for the treatment of patients with penicillin allergy. Clinically, the short time interval between ACPG treatments and the long duration of hospital stay increase the burden of patient care, such that many patients prefer the ceftriaxone regimen. However, there is a lack of clinical data comparing the efficacy of these two drugs. To our knowledge, this trial will be the first multicenter clinical trial comparing ACPG with ceftriaxone in a large number of patients in China with neurosyphilis. Findings of this trial may provide evidence to improve treatment guidelines.

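### Exclusion criteria 4, 6, 7 and half of 5 are events that arise after enrolment; as exclusions they contradict the plan's ITT, imputation, withdrawal and safety rules

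*Protocol article*

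**What the plan says.** All places are in the protocol article.

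- **Table 1, exclusion criteria 4 to 7.** Criterion 4 is "Serious adverse reactions during treatment". Criterion 5 is "Standardized treatment not carried out strictly according to the treatment regimen, or inability to follow up as required". Criterion 6 is "Patients who require the termination of treatment, for which the efficacy and adverse reactions cannot be evaluated, or patients who request withdrawal from the study". Criterion 7 is "Patients with incomplete clinical data that cannot be counted".
- **Inclusion and exclusion criteria, text.** "The attending physician of each patient will be responsible for assessing inclusion and exclusion criteria". The Blinding section says that clinicians and patients know the assigned group; outcome assessors and analysts can be masked.
- **Statistical analysis.** The ITT set is "all patients who met the inclusion criteria, were randomized, and started treatment". The per-protocol set is made up of compliant patients who completed the regimen. Non-inferiority requires consistent conclusions from the two sets. Missing primary outcomes are multiply imputed. The margin is 10 percentage points on the absolute difference.
- **Management of data and biological samples.** "Data from patients who did not complete follow-up and voluntarily withdrew from the study will be retained with other data".
- **Outcomes.** Withdrawal for any reason within 12 months is defined as an outcome. All adverse events after treatment and at each visit are to be recorded.
- **Interventions.** Patients whose mental disorder worsens or who have severe adverse events may discontinue treatment.

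**The concern.** An eligibility criterion should be decidable before allocation. Criterion 4 and the adherence half of criterion 5 need treatment to have begun. Criteria 6 and 7 will mostly be met during treatment or follow-up. Listed as exclusions, they can act only by taking out patients who are already in the trial, and the person applying them is not blinded.

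The patients concerned are those in whom treatment went badly or follow-up broke down. In a non-inferiority trial, losing failures from the analysis can make a worse treatment look acceptable. The usual safeguard, agreement between ITT and per-protocol results, does not help if the same failures are missing from both sets. Masked assessors and analysts do not help either, because they never see the removed patients. The adverse-event and withdrawal comparisons are exposed in the same way.

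**Working it through.** **1. The passages side by side**

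| Table 1 excludes | Elsewhere the article says |
|---|---|
| Serious reactions on treatment (4) | All adverse events are recorded (Adverse events); affected patients may discontinue (Interventions) |
| Regimen not strictly followed (5, first half) | Compliance defines the per-protocol set, not the ITT set (Statistical analysis) |
| Termination or withdrawal (6) | Withdrawn patients' data are kept (Management of data); withdrawal is an outcome (Withdrawal) |
| Incomplete data (7) | Missing primary outcomes are imputed (Statistical analysis) |

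The two columns cannot both be followed for the same patient. The second half of criterion 5, inability to attend follow-up, is different: it can be judged at screening.

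**2. The plan's own sample size, to fix the number per arm**

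- Events: (1 + 1.5)² / (1 − 1.5)² × 7.85 = 25 × 7.85 = 196.25, stated as 196.
- Participants: 196 / 0.85 = 230.6, stated as 230.
- After 20% loss: 230 / 0.80 = 287.5, so 288, taken to 5 × 58 = 290. With 1:1 allocation that is 145 per arm.

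The stated figures reproduce.

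**3. What removal of failures could do**

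Inputs from the article: success 85%, margin 10 points, two-sided 5% level, 145 per arm. Assumptions: ceftriaxone success is truly 75%, exactly at the margin; the test compares the lower limit of the unpooled 95% interval with −10 points; the shares of failures removed are chosen for illustration.

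If a share f of failures is removed from an arm with true success p, the apparent success is p / [p + (1 − p)(1 − f)] and the remaining number is 145 × [p + (1 − p)(1 − f)]. The chance of declaring non-inferiority is Φ[(d + 0.10) / SE − 1.96], where d is the apparent difference (ceftriaxone minus ACPG).

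Worked case, f = 0.25 in both arms:
- ACPG: 0.85 / 0.9625 = 0.883, with 139.6 patients left.
- Ceftriaxone: 0.75 / 0.9375 = 0.800, with 135.9 left.
- d = −0.083.
- SE = √(0.883 × 0.117 / 139.6 + 0.800 × 0.200 / 135.9) = 0.044.
- The chance is Φ(−1.57) = 5.8%.

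| Failures removed (ACPG / ceftriaxone) | Patients removed | Apparent difference | False non-inferiority: formula | Simulated (400,000 trials) |
|---|---|---|---|---|
| none | 0 / 0 | −10.0 | 2.5% | 2.6% |
| 25% / 25% | about 5 / 9 | −8.3 | 5.8% | 6.2% |
| 50% / 50% | about 11 / 18 | −6.2 | 16.4% | 17.8% |
| 0 / 25% | 0 / about 9 | −5.0 | 19.6% | 20.2% |

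With 115 per arm (230 / 2) the formula gives 2.5%, 5.3%, 13.9% and 16.4%.

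**4. The direction is not fixed**

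Suppose instead that 5% of all patients, every one a failure, leave each arm. Success becomes 0.85 / 0.95 = 89.5% and 0.75 / 0.95 = 78.9%, a difference of −10.5 points. The gap widens. Narrowing needs removal in proportion to failures, or removal mainly from the ceftriaxone arm.

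**The case against.** The best defence is that the analysis sets are defined in Statistical analysis, not in Table 1. The ITT definition names the inclusion criteria and does not mention the exclusion criteria. On that wording a treated patient with a serious reaction, poor adherence or missing data stays in. Imputation and the retention of withdrawn patients' data point the same way. This stands: the article does not show a plan to drop failures. It does not settle the matter, because Table 1 calls these patients excluded and nothing says which rule prevails.

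A reader might infer that serious reactions and withdrawals are bound to disappear from the results. The documents do not support that, since both are to be recorded or counted.

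A reader might also take the remark that "many patients prefer the ceftriaxone regimen" as evidence of bias towards ceftriaxone through patients who never start treatment. It is not. The remark concerns clinical practice in general, and refusals driven by it would fall mainly in the ACPG arm. If those refusers would have counted as failures, leaving them out raises the ACPG rate and makes non-inferiority harder to show. Requiring that treatment was started is also a common modified ITT, and the article states it openly.

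Lastly, the 20% loss in the sample size is an allowance for loss to follow-up. It is not permission to exclude failures and should not be read as the expected size of removal.

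**Conclusion.** The point holds as an internal contradiction with a harmful reading available. Criteria 4, 6, 7 and the first half of 5 are not eligibility criteria, and they conflict with the analysis, data-retention, outcome and safety sections. This is not detail left to a statistical analysis plan, because no such plan could obey both sides.

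If Table 1 prevails, failures can leave both analysis sets. Under the assumptions above, the chance of a false non-inferiority claim at the margin rises from 2.5% to between about 6% and 20%. Those figures rest on assumed removal shares and on a comparison in which every failure is otherwise counted. They show what the wording permits; they are not a forecast. The firm conclusion is that the error rate is not controlled while the wording stands, not that it must move in ceftriaxone's favour.

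The omission of randomised patients who never start is secondary. It deserves attention because the trial is open-label, so non-starting could differ by arm in either direction.

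**What to change.** 1. Limit the exclusion criteria to what is known before randomisation. Inability to attend follow-up may stay as a screening judgement.
2. State that patients who meet criteria 4 to 7 after randomisation remain in the ITT analysis in their assigned arm, with missing primary outcomes imputed as already planned, and remain in the safety and withdrawal comparisons.
3. Use non-adherence only to define the per-protocol set.
4. Remove criterion 7 as a ground for excluding randomised patients. The stated imputation covers the primary outcome only, so it should not be presented as covering all incomplete data.
5. Reconcile Table 1 with the Interventions section on discontinuation, so that the analysis status of patients who stop treatment is clear. The clinical rule is for the sponsor and investigators; none is proposed here.
6. Secondary: define ITT as all randomised patients, or call the present set modified ITT and report non-starters by arm.

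The cost is amendment wording and a few more patients with imputed outcomes. No change in sample size follows from this point.
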